#### 2.5.2. Assessments

The following information will be recorded for all potential patients as part of the screening assessments: Informed consent, inclusion/exclusion criteria, demography, including sex, race and age, medical history, and concomitant medication use (Table 3).

Each patient will be required to undergo the following assessments during the screening and run-in phases (Table 3) and treatment and follow-up phases (Table 4) at the study times indicated: Vital signs measurement, 12-lead electrocardiogram (ECG), body weight (kg) and height (m), physical examination, pregnancy test (female patients only), adverse event recording, total parenteral nutrition (TPN) use, handgrip strength using handgrip dynamometry, disability measured using the Rasch built Overall Disability Scale (RODS), ambulatory function measured using the 10 m walk test, gastrointestinal symptoms (abdominal pain, diarrhoea, disrupted swallowing, gas and bloating, gastroesophageal reflux, and nausea and vomiting) measured using the Patient-Reported Outcomes Measurement Information System (PROMIS) short form scales, distal sensory impairment and areflexia or motor strength using neurological examinations, MRI brain, abdominal ultrasound, nerve conduction studies and electromyography, neuro-ophthalmology and quality of life measured using EuroQol 5 Dimension (EuroQol-5D), Clinical Global Impression-Improvement Scale (CGI-I), Patient Global Impression of Change (PGIC), and visual analogue scale (VAS) for determining the severity of the patient’s most disabling symptom.

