### 2.6. Trial Endpoints

#### 2.6.1. Efficacy Endpoints

The primary efficacy endpoint will be the mean absolute change from baseline in body mass index (BMI) at 24 months. The secondary efficacy endpoints will be the mean absolute change from baseline in BMI at Day 63 and 3, 6, 9, 12, 15, 18, and 21 months, plus the change from baseline at 63 days and 3, 6, 9, 12, 15, 18, 21, and 24 months in: (i) The proportion of patients who require TPN; (ii) Handgrip dynamometry; (iii) RODS; (iv) 10 m walk test; (v) EuroQo-5D; (vi) CGI-I; (vii) PROMIS short form scales; (viii) PGIC; (ix) Neurological examination tests; and (x) VAS for the most disabling symptom.

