Neurological examination		X		X
MRI (brain)		X		X
Abdominal ultrasound		X		X
Nerve conduction and electromyography ^5^		X		X
Neuro-ophthalmological assessment		X		X
FGF-21, GDF15, and other markers of mitochondrial condition		X		X

^1^ For adult patients, height will be measured at the beginning of run-in period. For juvenile patients, height will be measured with weight at all time points. ^2^ Female patients only; pregnancy test at Day 0 (Treatment Cycle 1) to be conducted prior to study drug administration. ^3^ Serum biochemistry: Alanine aminotransferase, aspartate aminotransferase, alkaline phosphatase, albumin, gamma glutamyl transferase, sodium, potassium, chloride, calcium, magnesium, inorganic phosphate, glucose (non-fasting), urea, uric acid, total bilirubin, direct bilirubin, creatine kinase, iron, ferritin, folate, vitamin b12, total protein, cholesterol (including total, low density lipoprotein, and high density lipoprotein), triglycerides, lactate dehydrogenase, c reactive protein, and creatine kinase. Haematology: white blood cell count, red blood cell count, red cell distribution width, haemoglobin, haematocrit, mean cell volume, mean cell haemoglobin, mean cell haemoglobin concentration, platelet count, white blood cell differential, international normalised ratio, CD4+, and CD8+. ^4^ At screening the investigator and patient will identify the patient’s most disabling symptom. ^5^ Sensory bilateral nerves: Median, ulnar, radial, sural, and superficial peroneal; motor bilateral nerves: Median, ulna, common peroneal, and post tibial; EMG: Dorsal interosseous, tibialis anterior, and gastrocnemius bilateral muscles.

**Table 4 jcm-08-01096-t004:** Schedule of assessments during the treatment and follow-up phases.

Assessment	Study Day																	
	0 TC 1	1	7	14	21 TC 2	22	28	35	42 TC 3	43	49	56	63 TC 4	64	70	77	Every 2–4 Weeks up to 24 Months	Follow-Up 90 Days Post-Dose
Pregnancy test ^1^	X						X					X					X	X
RBC count					X				X								X	
Administration of Study Drug	X				X				X			X					X	
Adverse event recording	Ongoing during the study																	
Concomitant medication ^2^	Ongoing during the study																	
Vital signs	X	X			X	X			X	X			X	X	X	X	X	X
12-lead ECG	X	X			X	X			X	X			X	X	X	X	X	X
Clinical laboratory evaluations ^3^	X		X		X	X									X	X	X	X
Physical examination					X										X	X	X	X
Anti-TP antibody/neutralising antibodies	X								X				X				X	X

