Plasma thymidine and deoxyuridine			X	X	X		X	X	X		X	X	X		X	X	X ^4^	X
Urine thymidine and deoxyuridine	X		X	X	X		X	X	X		X	X	X		X	X	X ^5^	X
Body weight and height																	X	X
BMI																	X	X
Handgrip dynamometer													X				X	X
RODS													X				X	X
10-metre walk test													X				X	X
EuroQol-5D													X				X	X
PGIC													X				X	X
CGI-I													X				X	X
PROMIS													X				X	X
VAS symptom													X				X	X
TPN use													X				X	X
Neurological examination																	X	X
MRI (brain)																	X ^6^	X
Abdominal ultrasound																	X ^6^	X
Nerve conduction and electromyography ^7^																	X ^6^	X
Neuro-ophthalmological assessment																	X ^6^	X
FGF21, GDF15, and other markers of mitochondrial condition		X	X	X	X	X	X	X	X	X	X	X	X	X	X	X	X	X

^1^ Female patients only will be assessed at every 4 weeks. ^2^ Medication will be assessed for potential mitochondrial toxicity. ^3^ As reported in Table 4. ^4^ For the first 6 months, patients will return for an additional analysis of plasma thymidine and deoxyuridine at 7 days post-dose of every other treatment cycle. For rest of dosing, patients will return for an additional analysis of plasma thymidine and deoxyuridine at 7 days post-dose once every 4 treatment cycles. ^5^ 24 h urine collection for creatinine, thymidine, and deoxyuridine excretion will start from 6 days post-dosing for 24 h at every 4 treatment cycles. ^6^ Performed at 12 and 24 months. ^7^ As reported in Table 3. TC—treatment cycle.

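### Change in BMI and in neurological examination at Day 63 are named efficacy endpoints, but Table 4 schedules neither measurement on that day

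*Protocol article*

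**What the plan says.** Section 2.6.1 (Efficacy Endpoints) makes the 24-month change in BMI the primary efficacy endpoint. Among the secondary endpoints it lists the "mean absolute change from baseline in BMI at Day 63 and 3, 6, 9, 12, 15, 18, and 21 months". It continues "plus the change from baseline at 63 days and 3, 6, 9, 12, 15, 18, 21, and 24 months in" ten further measures, one of which is item "ix) Neurological examination tests".

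Section 2.5.2 (Assessments) states when data are collected: during the "treatment and follow-up phases (Table 4) at the study times indicated". Table 4 therefore governs on-treatment measurement.

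Table 4 has 18 columns. Sixteen are individual study days from 0 to 77, and Day 63 is one of them. The last two are "Every 2–4 Weeks up to 24 Months" and the follow-up visit 90 days after dosing. The rows "Body weight and height", BMI and "Neurological examination" carry marks in those last two columns only. The row "Handgrip dynamometer" and eight others carry a mark on Day 63 as well.

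**The concern.** An endpoint defined at a given day needs a measurement on that day. For BMI and the neurological examination, the endpoint list names Day 63 but the schedule provides nothing to compute it from. Values that were never collected cannot be recovered at analysis.

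BMI is also the variable on which the efficacy case rests. Section 2.8.3 plans to set BMI change against plasma and urine thymidine and deoxyuridine, and to report by dose the percentage of patients reaching the weight-gain threshold. The metabolites are sampled repeatedly between Day 7 and Day 77, while Treatment Cycles 1 to 4 are given at Dose Level 1 or 2 (Section 2.3). With no weight scheduled in those 11 weeks, there is nothing to pair with the metabolite values.

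**Working it through.** No sample-size or error-rate figure is involved. The check compares the endpoint time points in Section 2.6.1 with the marks in Table 4.

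**Step 1: columns.** The header reads Days 0, 1, 7, 14, 21, 22, 28, 35, 42, 43, 49, 56, 63, 64, 70 and 77, then the 2–4-weekly column, then follow-up: 16 + 2 = 18. Day 63 is column 13.

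**Step 2: are the rows intact?** The rows for weight and height, BMI, neurological examination, handgrip, TPN use and VAS each split into 18 cells, matching the header. No cell was dropped or shifted when these rows were read from the PDF.

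**Step 3: marks by row.**

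| Measure with a Day 63 endpoint | Marks, Day 0 to Day 77 | Later marks |
|---|---|---|
| BMI (and its source row, weight and height) | none | 2–4-weekly, follow-up |
| Neurological examination | none | 2–4-weekly, follow-up |
| Handgrip, RODS, 10 m walk, EuroQol-5D, PGIC, CGI-I, PROMIS, VAS, TPN use | Day 63 | 2–4-weekly, follow-up |

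Section 2.6.1 names 1 + 10 = 11 measures at Day 63. Nine are scheduled that day, and 11 − 9 = 2 are not.

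**Step 4: could the 2–4-weekly column cover Day 63?** No. Day 63 has its own column, the 2–4-weekly column comes after Day 77, and the flexible phase starts at Day 78 (Section 2.3 and the Figure 2 legend). The earliest scheduled on-treatment BMI or neurological value is thus at least 78 − 63 = 15 days late.

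**Step 5: could another row supply the value?** Adult height is taken once at the start of run-in (Table 3, footnote 1), so a single weight on Day 63 would give an adult's BMI, but no weight is scheduled. Physical examination is not marked on Day 63 either.

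**Step 6: extent.** Baseline is intact, because Table 3 marks BMI at three run-in visits, including Day −1 to 0. The gap runs from that visit to Day 77, which is 77 / 7 = 11 weeks. The endpoints lost are 1 of 8 secondary BMI time points (Day 63 plus seven from month 3 to month 21) and 1 of 9 neurological time points (Day 63 plus eight from month 3 to month 24). For those two, the share of adults without a scheduled value is 12 of 12.

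**The case against.** The main objection is that the damage is small. The primary endpoint, its run-in baseline and every time point from month 3 onwards are untouched, and month 3 falls only about four weeks after Day 63. The analyses are mainly descriptive, there is no power calculation, and no stated decision uses Day 63 BMI or neurological findings. The early dose steps depend on plasma metabolites, which are well sampled. All of this stands and limits the consequence.

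The blanks may also be clerical. Table 4 shows other slips: study drug administration is marked under Day 56, whereas the column header and Section 2.3 place Treatment Cycle 4 on Day 63 (these too must be reconciled), and footnote 3 refers the reader to Table 4 itself for a list that stands in Table 3. A clerical cause is plausible but cannot be confirmed. A one-column shift would not explain rows that have no mark anywhere from Day 0 to Day 77.

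Finally, a site could take an unscheduled weight, and the full protocol is not shown. The contradiction nevertheless lies between two parts of this article. It is not a detail left to a longer document.

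**Conclusion.** The point holds. Under the schedule as printed, the Day 63 changes in BMI and in neurological examination cannot be computed for any of the 12 adults, and no weight is scheduled after the Day −1 to 0 visit until the phase starting on Day 78. The loss is one early secondary time point for each of two measures, plus any early pairing of BMI with metabolites.

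This rests on one assumption: that sites follow Table 4, as Section 2.5.2 says they will, and take no unscheduled measurements. The documents do not show whether the endpoint list or the table reflects the intention.

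**What to change.** Make Section 2.6.1 and Table 4 agree, in one of two ways for each measure:

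- Mark weight/BMI and neurological examination in the Day 63 column of Table 4.
- Remove Day 63 from the endpoint list for whichever measure is not wanted that early.

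For BMI the first option is preferable, since it is the primary efficacy variable. Patients already attend on Day 63 for nine other efficacy measures, so the added burden is one weighing and one clinical examination at an existing visit.

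If weight is added, the schedule should also say that it is taken before blood collection. This is a measurement refinement, separate from the contradiction. Section 2.5.1 has 120–360 mL removed on treatment mornings. At an assumed blood density of 1.06 kg/L that is 0.120 × 1.06 = 0.13 kg to 0.360 × 1.06 = 0.38 kg, which is not negligible beside the roughly 0.5 kg that the Discussion equates with the 0.2 kg/m² threshold.

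The cost is a correction to a table or a sentence. Section 2.13 reports that recruitment has not opened, so it can be made before any data are lost.

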#### 2.6.2. Safety Endpoints

The clinical safety of EE-TP will be evaluated by: (i) The incidence, frequency, and severity of adverse events (or treatment-emergent adverse events); (ii) The incidence of laboratory abnormalities, based on haematology, serum biochemistry, and urinalysis test results; (iii) Vital sign measurements (systolic and diastolic blood pressure, pulse rate, respiratory rate, and body temperature); (iv) 12 lead ECG parameters; (v) Physical examination findings; and (vi) The use of concomitant medication(s).

### 2.7. Sample Size

The sample size for this study is dictated by the rarity of the condition and not by any quantitative statistical considerations or formal sample size calculations. At least 12 adult treatment naïve patients will be treated in this study, with the option to enrol an additional 8 juvenile patients, beyond this original set of 12 patients.

### 2.8. Statistical Analyses

Statistical analyses will be primarily descriptive. Analyses will be performed using Statistical Analysis Software^®^ (Version 9.2 or higher, SAS Institute, Cary, NC, USA). For continuous data, summary statistics will include the arithmetic mean, arithmetic standard deviation, median, lower and upper quartiles, plus minimum, maximum, and number. For log normal data, summary statistics, including the geometric mean and geometric coefficient of variation, will also be presented. For categorical data, frequency counts and percentages will be presented. Data listings will be provided for all patients up to the point of withdrawal, with any patients excluded from the relevant population indicated. For the calculation of summary statistics and statistical analysis, unrounded data will be used.

For each study participant the change from baseline will be calculated by subtracting their mean baseline value from the value at the specific time point. The mean change from baseline will be derived as the arithmetic mean of all individual patients’ change from baseline values.

#### 2.8.1. Safety Data Analysis

A baseline sign and symptom will be defined as an adverse event that starts after the patient has provided written informed consent and resolves prior to the first treatment cycle. It will also be defined as an adverse event that starts prior to the first treatment cycle and does not increase in severity after dosing. A treatment emergent adverse event will be defined as an adverse event that occurs post-dose or that is present pre-dose and becomes more severe post-dose. Treatment emergent adverse events will be summarised by dose level, maximum severity, and relationship to the study drug. The frequency of treatment emergent adverse events plus the number and percentage of patients experiencing a treatment emergent adverse event will be summarised by dose level, the Medical Dictionary for Regulatory Activities system organ class, plus preferred term. A frequency summary will be presented by day of onset across the multiple dosing period. 

Vital signs, serum biochemistry, haematology, and urinalysis data will be summarised by dose level, together with changes from the baseline. All serum biochemistry, haematology, and urinalysis data outside the clinical reference ranges will be listed by parameter and treatment. ECG data, including QTc, QTcB, QTcF, the PR and QT intervals, QRS duration, and heart rate, will be obtained directly from the 12-lead ECG traces. The ECG data will be summarised by dose level. Values for ECG parameters outside the clinical reference ranges will be indicated on the individual patient data listings. Physical examination and concomitant medication data will be listed.

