Patients with MNGIE usually present during the second decade of life, although patients have presented as early as five months and as late as the fifth decade; the average age at diagnosis is 18.5 years [12]. The relatively late onset for a condition present at birth is thought to be due to the progressive accumulation of mtDNA defects, with the disease becoming apparent once the number of affected mitochondria reaches a critical threshold level. The disease is a multi-system disorder, and has a characteristic, although by no means universal, clinical presentation. Patients typically present with gastrointestinal symptoms including early satiety, nausea, dysphagia, gastroesophageal reflux, postprandial emesis, episodic abdominal pain, episodic abdominal distention, and diarrhoea. These symptoms are secondary to alimentary dysmotility caused by degeneration of the alimentary autonomic nervous system [2]. Patients generally have a thin body habitus with reduced muscle mass and cachexia. Episodes of frank intestinal pseudo obstruction may occur, and some patients develop a hepatopathy with liver steatosis and cirrhosis. Progressive external ophthalmoplegia and peripheral sensorimotor polyneuropathy are invariable. The latter affects the lower limbs initially and is typically demyelinating. On magnetic resonance imaging (MRI) there is, in the majority of cases, leukoencephalopathy with diffuse increased T2 signal in the deep white matter of the cerebral hemispheres, but this is generally believed to be asymptomatic [5,12].

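### An event present before first dosing is treatment-emergent only if it becomes more severe, so a continuing symptom that merely becomes more frequent stays out of the treatment-emergent tables

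*Protocol article*

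**What the plan says.** Section 2.8.1 (Safety Data Analysis) sorts adverse events around the first dose into two classes, each with two limbs.

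- Baseline sign or symptom: either "an adverse event that starts after the patient has provided written informed consent and resolves prior to the first treatment cycle", or "an adverse event that starts prior to the first treatment cycle and does not increase in severity after dosing".
- Treatment-emergent adverse event: "an adverse event that occurs post-dose or that is present pre-dose and becomes more severe post-dose".

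The tables then follow from the second class. "Treatment emergent adverse events will be summarised by dose level, maximum severity, and relationship to the study drug". Event counts and patient percentages by dose level, system organ class and preferred term are also given for treatment-emergent events. A third table comes directly after these: "A frequency summary will be presented by day of onset across the multiple dosing period". It names no other set of events. The section announces no summary of baseline signs; Section 2.8 provides data listings for all patients.

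Three other statements set the context. Section 2.1 puts safety and tolerability among the primary objectives. Section 2.3 describes an open-label trial without a control, in which every patient receives EE-TP. The Introduction lists among the typical presenting symptoms "postprandial emesis, episodic abdominal pain, episodic abdominal distention, and diarrhoea".

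**The concern.** An episodic symptom can get worse in two ways: each episode becomes more severe, or episodes come more often. For an event that already exists at first dosing, the definition recognises only the first. A patient whose mild abdominal pain was occasional in run-in and frequent on treatment, logged throughout as one mild ongoing event, is classed exactly like a patient whose pain did not change.

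What is at stake is the main safety output. The treatment-emergent tables are where a reader looks for tolerability by dose level and by relationship to study drug. With no comparator arm, no control rate exists against which a rise in frequency could show up by another route. In this disease many patients can be expected to enter with gastrointestinal symptoms, so the rule for pre-existing events is not a corner case.

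**Working it through.** The protocol article attaches no figure to this rule and reports no sample size calculation (Section 2.7), so there is no number to reproduce. The check applies the definitions in Section 2.8.1 to each way in which a pre-existing symptom might be recorded.

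| Symptom after first dosing | How recorded | Limb that applies | Class |
|---|---|---|---|
| A. Same severity, same frequency | one event spanning first dose | began before Cycle 1, severity not increased | baseline sign |
| B. Same severity, more frequent | one event spanning first dose | began before Cycle 1, severity not increased | baseline sign |
| C. More severe, whatever the frequency | one event spanning first dose | present before dosing, more severe after | treatment-emergent |
| D. Same severity, more frequent | each episode a separate event | episodes resolved before Cycle 1: baseline; episodes arising after dosing: post-dose limb | later episodes treatment-emergent |

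Two results follow.

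1. A and B receive the same class. For an event spanning first dose, the rule cannot tell an unchanged symptom from one that has become more frequent, and B contributes nothing to the treatment-emergent tables.
2. In D the post-dose limb of the same definition captures the episodes at any severity. The loss is therefore confined to B.

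Size. Inputs: 12 adult patients (Sections 2.4 and 2.7), up to 8 further juvenile patients (same sections), and all patients starting at Dose Level 1 (Section 2.3). If all 12 adults are dosed, the Dose Level 1 denominator is 12.

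- One patient in case B: 1/12 = 8.3 percentage points on the percentage for that preferred term.
- Two patients: 2/12 = 16.7 points.
- If juveniles are pooled into the same safety table: 1/(12 + 8) = 1/20 = 5.0 points per patient.

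At Dose Levels 2 and 3 the denominators can only be the same or smaller, so the effect per patient is the same or larger. How many patients would fall into case B cannot be derived from the document.

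**The case against.** The strongest reply is that the loss depends on a recording convention that the article does not state. If sites log each episode as its own event, post-dose episodes are counted. Conventions for recurrent events, the severity scale and the adverse event form belong to the full protocol or the analysis plan, which are not shown. That stands: the absence of a convention is no fault here, and the point has to be conditional. What remains is the stated rule for an event that does span first dose, and that rule leaves frequency out.

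A second reply is that severity may be rated with frequency in mind, so a marked rise in episodes would be graded up and so qualify. This is possible, and would shrink case B, but nothing in the article says so.

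Third, the signal would be seen elsewhere. Section 2.5.2 has "gastrointestinal symptoms (abdominal pain, diarrhoea, disrupted swallowing, gas and bloating, gastroesophageal reflux, and nausea and vomiting) measured using the" PROMIS short forms, taken three times in run-in (Table 3), at Day 63 and later (Table 4). There are also the listings, and the monitoring committee reviews adverse events generally (Section 2.9). These soften the loss. But PROMIS is a secondary efficacy endpoint (Section 2.6.1), with no attribution to study drug, and neither listings nor committee review changes the tabulated treatment-emergent incidence.

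Fourth, the disease is progressive, so a frequency criterion would also admit natural worsening. So does the existing severity criterion. Treatment-emergent status describes timing, and the tables already separate events by relationship to study drug.

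Finally, how a long-standing condition collected as medical history becomes an adverse event is not shown, which limits what can be said about how often case B arises.

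**Conclusion.** The point holds in a limited form. For an event already present before the first treatment cycle, a rise in severity is the only route to treatment-emergent status. A continuing event that becomes more frequent at unchanged severity is therefore a baseline sign and is missing from the treatment-emergent tables. This rests on two conditions: the symptom is recorded as one event across first dosing, and its severity rating does not move with frequency. Under those conditions each affected adult shifts a Dose Level 1 percentage by about 8 points, and the number affected is unknown. It is worth correcting, but it invalidates no figure in the article.

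Four stronger readings are tempting, and the document does not support them.

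- That every increase in an episodic symptom disappears from the tables. The post-dose limb captures separately recorded episodes.
- That the rule contradicts Section 2.6.2, which lists "The incidence, frequency, and severity of adverse events (or treatment-emergent adverse events") as a safety measure. Frequency there is naturally read as the number of events, which Section 2.8.1 does tabulate; it does not promise the episode rate within one event.
- That worsened pre-existing events cannot be placed in the day-of-onset table. The article does not say which date they carry, and an analysis plan would ordinarily settle that.
- That the bias can be put as a large numerical contrast between a worsened and an unchanged patient. Any such contrast needs assumed episode rates and compares two different recording conventions.

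**What to change.** Amend both sentences in Section 2.8.1 so that they remain complementary.

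- Treatment-emergent: the event arises after dosing, or it is present before dosing and increases in severity or in frequency afterwards.
- Baseline sign, second limb: the event began before the first treatment cycle and increases in neither severity nor frequency after dosing.

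The first limb of the baseline definition needs no change. The 90-day run-in supplies a pre-treatment period against which the investigator can judge a change in frequency.

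The cost is a wording change to two sentences. Section 2.13 states that the trial was not yet recruiting, so at that stage it could be made before any data existed. The small downside is that the treatment-emergent count may rise slightly, including some events that reflect progression of the disease; the existing breakdown by relationship to study drug helps the reader to interpret them.
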